### Safety and ethical considerations

We have obtained permission from the European Organization for Research and Treatment of Cancer to use the QoL questionnaires, EORT QLQ-C30 and QLQ-BR23 and from the EuroQoL Research Foundation to use the EQ-5D-5 L. We are using a version of HADS that has been validated by this research group [23].

Eligible patients will be informed verbally by trained research personal as well as in writing, and written informed consent will be obtained prior to enrollment. Patients may withdraw from the study at any time, during recruitment or follow-up, and all data collected will be treated as confidential. All participating hospitals have staff available to answer any questions that the patient or family members may have about the research.

Ethics Committe of each center approved the study. This study is registered with Clinical Trials.gov (identifier: NCT02439554).

### Follow-up

Regular follow-up visits will be performed up to 2 years at all 13 participating hospitals. In addition, a 5-year follow-up visit is also planned in all participating hospitals.

### Sample size calculation

We estimated the sample size based on the objective related to the creation and validation of a predictive model for which a relatively large sample size is required. The literature on prediction models indicates that a minimum of 10 outcome events are needed per predictor (relapse) [24]. Our aim is to include a limited but comprehensive list of variables (likely, not less than 10), in the multivariate regression models. Given this, we estimated that we needed at least 100 events of the dependent variable in the sample in order to ensure that the regression model converges adequately. It has been reported [25] that 7% of patients with breast cancer relapse within the first 2 years and considering this rate, we calculated the estimated sample size. Nevertheless, so far, based on 1456 patients, the relapse rate has been 4%, implying that no more than six variables should be included in the predictive models. We included all consecutive new cases until the sample size was achieved.

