**Methods:**

Prospective cohort study involving 13 hospitals in Spain with a follow-up period of up to 5 years after diagnostic biopsy. Eligibility criteria: Patients diagnosed with breast cancer between April 2013 and May 2015 that have consented to participate in the study. Data collection: Data will be collected on the following: pre-intervention medical history, biological, clinical, and sociodemographic characteristics, mode of cancer detection, hospital admission, treatment, and outcomes up to 5 years after initial treatment. Questionnaires about quality of life (EuroQoL EQ-5D-5 L, the European Organization For Research And Treatment Of Cancer Core Quality Of Life Questionnaire EORTC QLQ-C30 join to the specific breast cancer module (QLQ-BR23), as well as Hospital Anxiety and Depression Scale were completed by the patients before the beginning of the initial treatment and at the end of follow-up period, 2 years later. The end-points of the study were changes in health-related quality of life, recurrence, complications and readmissions at 2 and 5 years after initial treatment. Statistical analysis: Descriptive statistics will be calculated and multivariate models will be used where appropriate to adjust for potential confounders. In order to create and validate a prediction model, split validation and bootstrapping will be performed. Cost analysis will be carried out from the perspective of a national health system.

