### Statistical analysis

- Descriptive statistics: Mean and standard deviations for continuous variables (or median and interquartile ranges, when the observed variables do not follow a normal distribution) and frequencies and percentages for qualitative variables.-Bivariate analysis:The Student’s t-test or the non-parametric Wilcoxon test (for non-normal distributions) will be applied for two-level outcomes, and ANOVA analysis or a Kruskal–Wallis test (for non-normal distributions) where there are three or more categories in the outcome. Otherwise, for categorical variables, the Chi-square test (or Fisher’s Exact method, where required) will be used. Multivariate models will be used where appropriate to adjust for confounders.-Creation and validation of predicitive models:. Participants will be randomly divided into two groups: the derivation (60%) and validation (40%) cohorts. The study unit will be the patient (each patient being included only once). The predictive model will be created with the derivation group (group 1). Initially, univariate analyses will be performed, to identify variables related to the selected outcomes. Variables with a *p* < 0.20 will be entered into a multivariate logistic regression model, when outcome variables are dichotomous (mortality, re-admissions or relapse, major complications). Statistically significant variables will be included in the final model. Based on its estimated contribution in the multivariate logistic regression model, a score will be assigned to each variable. From this, a severity risk score will be created with the receiver operating characteristic curve. One cut-off point will be selected, namely, that giving the best balance between sensitivity and specificity. For the continuous outcomes (changes in health-related quality of life), a general lineal model will be used. The validity of the model and the score will be tested in the validation sample (group 2) and also in the retrospective sample (group 3). We will calculate the sensitivity, specificity, and area under the receiver operating characteristic curve (AUC), and *p* values for comparisons of AUCs between the groups. The models will be calibrated using the Hosmer-Lemeshow test. A multilevel analysis will be performed with patients (level 1) nested within hospitals (level 2).

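### The six-predictor limit counts relapses in all 1456 women, but the model is built in a random 60%, where the plan's own 10-events rule allows about three predictors at the current relapse rate

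*Protocol article*

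**What the plan says.** The protocol's section on sample size calculation bases the study size on the prediction model for relapse. It adopts a rule of at least ten relapses per predictor, expects to need ten or more predictors, and so reasons that "we estimated that we needed at least 100 events of the dependent variable in the sample". It takes a 7% two-year relapse rate from the literature for this purpose. It then updates the limit from the data in hand: "Nevertheless, so far, based on 1456 patients, the relapse rate has been 4%, implying that no more than six variables should be included" in the models.

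The statistical analysis section says: "Participants will be randomly divided into two groups: the derivation (60%) and validation (40%) cohorts". The model is created in the derivation group alone. It is tested in the 40% validation group and in the sample from the earlier retrospective study. The listed measures are sensitivity, specificity, AUC and p values comparing AUCs between groups, and the section adds that "The models will be calibrated using the Hosmer-Lemeshow test". The abstract says that "split validation and bootstrapping will be performed".

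**The concern.** An events-per-predictor rule protects the fit of a model only if the events counted are those in the data to which the model is fitted. The sample size section counts relapses in the whole cohort, while the analysis section fits the model to 60% of it. Nothing in the document carries the 60% into the event count, so a team that follows both sections can fit six predictors and believe that the rule is met when it is not.

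The study size was justified by this model, and the discussion intends the resulting rules for electronic health records and individual decisions. Too many predictors for the events available gives unstable coefficients and an optimistic apparent AUC. The internal validation group, with fewer relapses still, is poorly placed to show this.

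**Working it through.** **Inputs from the protocol.** Rule: 10 relapses per predictor. Planned relapse rate 7%, interim rate 4%, 1456 women (sample size calculation). Derivation share 0.60 and validation share 0.40 (statistical analysis). 1629 recruited (discussion).

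**1. The plan's own figures.**
- Planning target: 100 / 0.07 = 1429 women, close to the 1456 obtained; 1456 x 0.07 = 101.9 relapses.
- Revised limit: 1456 x 0.04 = 58.2 relapses; 58.2 / 10 = 5.8. The stated six therefore needs all 1456 women and rounding up. A limit rounded down is 5.

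**2. The same rule in the derivation group.** Relapses = N x rate x 0.60; limit = relapses / 10, rounded down.

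| N | Rate | All relapses | Derivation relapses | Limit |
|---|---|---|---|---|
| 1456 | 4% (interim) | 58.2 | 34.9 | 3 |
| 1456 | 3.5% | 51.0 | 30.6 | 3 |
| 1456 | 4.5% | 65.5 | 39.3 | 3 |
| 1629 | 4% | 65.2 | 39.1 | 3 |
| 1456 | 7% (planned) | 101.9 | 61.2 | 6 |

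The 3.5% and 4.5% rows allow for rounding of the published 4%. Six predictors on 34.9 relapses give 34.9 / 6 = 5.8 per predictor; ten give 3.5.

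**3. What six or ten predictors would need.**
- Six predictors need 60 derivation relapses: 60 / (0.60 x 0.04) = 2500 women at 4%, or a rate of 60 / (0.60 x 1456) = 6.9% in the present cohort.
- Ten predictors need 100 derivation relapses: 100 / (0.60 x 0.07) = 2381 women at the planned 7%.

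**4. The validation group.** 1456 x 0.04 x 0.40 = 23.3 relapses. The AUC values below are assumptions, as the protocol gives none. Standard errors are Hanley-McNeil, for (relapses / no relapse).
- AUC 0.75, validation (23/559): SE 0.060, 95% half-width 1.96 x 0.060 = 0.12. At AUC 0.70 and 0.80 the half-widths are 0.12 and 0.11.
- AUC 0.75, all women (58/1398): SE 0.038, half-width 0.07.
- Comparing AUCs: derivation 0.75 (35/839), SE 0.048; validation 0.65 (23/559), SE 0.063. SE of the difference = sqrt(0.048^2 + 0.063^2) = 0.080. z = 0.10 / 0.080 = 1.25, so two-sided 5% power is about 24%. For a drop to 0.70 it is about 10%.

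**The case against.** **The 4% is interim.** The protocol says so, and five-year data are intended if funding allows. More relapses would raise the limit. This stands as a qualification: 35 and 23 are projections at the current rate, not final counts. But six predictors need about 6.9%, and the protocol itself derives its six from the 4%.

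**Six is a ceiling.** The plan does not commit to using six, so it permits a breach of its rule and does not make one certain. The ceiling is still twice what the rule allows in the derivation group.

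**The 40% group is not the only check.** This also stands. The model is tested in the retrospective sample too, so it would be wrong to infer that validation as a whole cannot reveal overfitting. That cohort has 1086 women, all from a screening program and none symptomatic, so it does not cover the full target population. Its relapse count is not given, so its precision cannot be worked out here.

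**Three stronger readings are tempting, and the document does not support them.**
- A reader might remove stage 0 and stage IV women and quote about 52 relapses. In situ cancers are excluded only from the survival analysis, the relapse model is logistic, and no text excludes stage IV from it. Nor would relapses necessarily fall in proportion to the women removed.
- A reader might infer that a non-significant AUC difference will be taken as proof of validity. The plan sets no such criterion and lists other measures beside that p value.
- A reader might object that the bootstrap is not described. The abstract promises it, and a condensed article may leave the details to the full plan.

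**Conclusion.** The point holds as an inconsistency between two sections. The rule is applied to the whole cohort and the model is fitted to 60% of it, and no text reconciles the two. At the interim rate the derivation limit is 3 predictors, not six, whether the 4% stands for 3.5% or 4.5% and whether 1456 or 1629 women are counted at 4%. The planning target was short for the same reason: 6 predictors at 7%, not ten.

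The low precision of internal validation is a consequence. Its size rests on the assumed AUCs and on the interim relapse count. No power was calculated for the Hosmer-Lemeshow test, so none is claimed.

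The calculation concerns the relapse model. The descriptive, cost and continuous quality-of-life analyses are not affected by it.

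**What to change.** Reconcile the abstract, the sample size section and the statistical analysis section before the relapse model is fitted.

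**Preferred.** Develop the relapse model on all eligible women. Validate it internally with the bootstrap already promised, repeating the univariate screening and variable selection in every resample. Keep the retrospective cohort as the external check, noting that it covers screening participants only. State the limit as 5 predictors (58 / 10, rounded down).

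**If the 60/40 split is kept.** State the limit as 3, and update it from the final number of relapses in the derivation group. Say also that the 100-event target referred to the whole cohort.

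**In either case.** Report AUC and calibration with confidence intervals, and do not rest the judgement of validity on the AUC-comparison p value or the Hosmer-Lemeshow test alone.

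The cost is a few sentences in three places and, for the preferred option, a short bootstrap program. No new data are needed. The price is a smaller stated number of predictors.

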### Design and setting

CaMISS-Prospective is an observational analytic prospective cohort study. All the patients have been consecutively selected between April 15, 2013 and May 20, 2015, from 13 hospitals in 4 Spanish regions (Andalusia, Canary Islands, Catalonia, and the Basque Country). All participant centers belongs to the Spanish National Services were primary care and hospital emergency departments are free. Regions and participating hospitals are listed in Table 2.

**Table 2 Tab2:** Patients recruited by area and hospital

Region	Hospital	Valid patients
Catalonia	Hospital del Mar, Barcelona	97
Basque Country	Hospital Galdakao-Usansolo, Bizkaia	197
	Hospital de Cruces, Bizkaia	246
	Hospital de Basurto, Bizkaia	125
	Hospital de Txagorritxu, Araba	229
	H.U. Donostia, San Sebastián, Gipuzkoa	245
	Instituto Oncológico, San Sebastian, Gipuzkoa	134
Andalusia	Hospital Costa del Sol, Malaga	80
	Antequera, Málaga	6
Canary Islands	Hospital Nuestra Sra de La Candelaria (Tenerife)	61
	Hospital Universitario de Canarias (Tenerife)	
	Complejo Materno-Insular (Gran Canaria)	36
	Clínica San Roque (Gran Canaria)	
Total		1456

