### Duration of the project

The project is planned to last for at least 3 years divides in recruitment (1 year) and follow-up (2 years), At least 6 months will be required to finish error correction process and database cleaning. In a second stage, it is envisaged that patients will be followed-up at 5 years after their diagnostic biopsy (but, as mentioned above, this depends on funding).

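### The six-variable limit rests on an undated crude 4% relapse rate set against a 2-year risk of 7%, and the one-year recruitment in the timetable conflicts with the 25 months actually taken

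*Protocol article*

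**What the plan says.** The sample size section of the protocol article takes from the literature that "a minimum of 10 outcome events are needed per predictor (relapse"), aims for about ten variables or more, and concludes that "we needed at least 100 events of the dependent variable in the sample". The rate used to turn events into patients has a time horizon: "7% of patients with breast cancer relapse within the first 2 years".

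The same paragraph then revises the model size: "so far, based on 1456 patients, the relapse rate has been 4%, implying that no more than six variables should be included". It does not say when this count was made, how long the women had been followed, or how many had a complete 2-year record.

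On entry, the design section states: "All the patients have been consecutively selected between April 15, 2013 and May 20, 2015". On timing, the duration section states: "The project is planned to last for at least 3 years divides in recruitment (1 year) and follow-up (2 years"), followed by at least 6 months of cleaning. The data collection section has medical records reviewed at 2 and 5 years after diagnosis. The statistical analysis section models relapse as a yes/no outcome by logistic regression.

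**The concern.** Two different quantities are treated as one. The 7% is a risk over a fixed 2-year window. The 4% is a proportion of all 1456 women at an unstated date. With staggered entry, a crude proportion rises with calendar time until the last woman completes her window, so an early 4% and a final 7% can both be true. The paragraph nevertheless reads the 4% as replacing the 7% and reduces the models from about ten variables to six.

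At stake is the size of the study's main prediction model. If the count was early, the limit is tighter than the protocol's own rule would require once the data are complete, and useful predictors could be left out.

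The duration section adds to the uncertainty. It still describes one year of recruitment, so it cannot be used to work out when 2-year follow-up is complete and the models can be fitted.

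**Working it through.** **Inputs.** Sample size section: 10 events per predictor, 100 events needed, 7% at 2 years, 4% of 1456 observed. Design section: entry from 15 April 2013 to 20 May 2015. Duration section: 1 year of recruitment, 2 years of follow-up, at least 6 months of cleaning.

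**The plan's own figures reproduce.**
- Plan: 100 / 0.07 = 1429 patients, close to the 1456 in hand.
- Revision: 0.04 × 1456 = 58 events; 58 / 10 = 5.8, stated as six. As 4% is itself rounded, 3.5% to 4.5% gives 51 to 66 events, or 5.1 to 6.6 predictors.
- If 7% held: 0.07 × 1456 = 102 events, or 10 predictors.

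The arithmetic is sound. The question is whether the 4% is a 2-year figure.

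**Length of entry.** 15 April 2013 to 20 May 2015 is 765 days; 765 / 30.4375 = 25.1 months, or T = 765 / 365.25 = 2.094 years.

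**What a true 7% would look like at an earlier count.** Assumptions, none of them given in the document: uniform accrual, constant hazard, no losses, each woman's clock starting at entry and her follow-up capped at 2 years.
- Hazard: h = −ln(0.93) / 2 = 0.0363 per year.
- At c years after the last enrolment (c below 2), follow-up before the cap is uniform between c and c + T. The expected crude proportion is
 [(2 − c) − (e^(−hc) − 0.93)/h + 0.07 × (c + T − 2)] / T.
- Worked at c = 0: [2 − 0.07/0.0363 + 0.07 × 0.094] / 2.094 = (0.0708 + 0.0066) / 2.094 = 0.037.

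| Months after last enrolment | Expected crude relapse | Events in 1456 |
|---|---|---|
| 0 | 3.7% | 54 |
| 3 | 4.5% | 65 |
| 6 | 5.1% | 75 |
| 12 | 6.2% | 90 |
| 24 | 7.0% | 102 |

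Events are the unrounded proportion × 1456 (for example 0.0447 × 1456 = 65). A reported 4% therefore agrees with a true 7% only if it was counted at or up to about 3 months after the last enrolment. Counted later, it points to a true rate below 7%. Counted after every woman had 24 months, it is simply the 2-year rate.

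**Timetable.** Recruitment of 25 months plus 24 months for the last woman gives about 49 months from first entry, that is 20 May 2017. With at least 6 months of cleaning, the total is at least about 55 months, to about November 2017. The duration section's components sum to 12 + 24 = 36 months before cleaning.

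**The case against.** Incomplete follow-up behind the 4% is not proved. The wording suggests an interim count, and the follow-up section puts the 2-year visits in the future. The abstract, however, describes the 2-year questionnaires in the past tense, and tenses are mixed throughout the article. If the count came after May 2017, the comparison with 7% is fair and the downward revision reasonable. Even before then, 4% fits 7% only in a narrow window. This stands, and it limits the conclusion to a conditional one. It does not remove the point, because the abstract's sentence concerns questionnaires rather than relapse, and without a cut-off date the reader cannot tell which case applies.

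The limit may also be read as a provisional ceiling. If it is too low, it does not cause overfitting, and more events later would allow more predictors. This stands too, and it is why the point is minor.

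Stronger readings are tempting. A reader might infer from the duration section that the project closes three years after the first entry and leaves about half the women without their 2-year window. The text does not support this: it gives three years as a minimum, allots two years to follow-up, and sets no closing or lock date. A reader might also infer that women recruited late would be recorded as relapse-free because their time had not elapsed, or that hospitals recruiting late would look better. But records are to be reviewed at 2 years after each woman's own diagnosis, and the table of hospitals gives counts without recruitment dates.

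**Conclusion.** The concern holds in a limited form and is minor. A rate with a 2-year horizon is replaced by a crude proportion with no stated horizon, and a model-size limit is drawn from it. Depending on when the count was made, the eventual number of relapses in 1456 women could stay near 58 (about six predictors by the protocol's rule) or be as high as 102 (ten) if the planning rate is right. The upper end assumes the 7% itself, and the intermediate values rest on uniform accrual, constant hazard and no losses. The document does not allow a choice between these.

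Separately, and without any assumption, the one-year recruitment in the duration section contradicts the 25 months in the design section. This is an outdated timetable, not a planned loss of follow-up.

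**What to change.** - Set the number of predictors from relapses within 24 months in the data used to fit the model, counted after the last woman's 24-month review (20 May 2017, taking her clock from the last recruitment date). Under the statistical analysis section the fitting data are the 60% derivation group, so the count that matters is smaller than the one for all 1456 women: at 4%, 0.6 × 58 = 35.
- If a rate is quoted before then, give a Kaplan-Meier 24-month estimate with its cut-off date in place of the crude 4%.
- Reconcile the duration section with the design section: recruitment about 25 months, complete 2-year follow-up about 49 months from first entry, then at least 6 months of cleaning.
- State that the 2-year models are fitted only after that point.

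The cost is a text correction and a longer stated project duration. No new patients or data are needed.

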## Methods/Design

### Aim

The specific study objectives (which are set out in detail in Table 1) are, in brief: 1. to assess outcomes related to a) process of care (early diagnosis, access to health care and screening programs, delays in diagnosis, and variability in treatments), and b) patients (sociodemographic and clinical characteristics, including biomarkers, and patient-reported outcomes, such as quality of life and emotional state); 2. to create and validate prediction models (for changes in quality of life, relapse and death); and 3. to assess the costs associated with breast cancer care and its potential variations between Spanish regions.

**Table 1 Tab1:** Objectives

1. Outcomes assessment	2. Creation of predictive models	3. Health services evaluation in breast cancer patients in Spain
To describe and analyse variability in outcomes by mode of detection, hospital, region and surgeon	• To create and validate predictive rules for relapse, mortality and complications	• To estimate the average costs of breast cancer care in Spain
To describe and analyse variability in the diagnostic process and treatment	• To identify risk factors for poor health-related quality of life 2 years after treatment	• To investigate differences between Spanish regions
To explore potential inequalities by age, education and socioeconomic level	• To validate our predictive rules for relapse, mortality and complications in a retrospective sample of patients from early detection programs	• To identify the most efficient process and treatments in breast cancer
To evaluate the impact of first hospital care (urgent or scheduled) and of delays on relapse, metastasis and death		

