### Study population

Women older than 18 years with an incident breast tumor will be included. The breast cancer diagnosis considered will be that reached after a biopsy of the tumor, including cases of ductal carcinoma in situ, invasive ductal carcinoma, tubular carcinoma, mucinous carcinoma, papillary carcinoma, cribriform carcinoma, invasive lobular carcinoma and lobular carcinoma in situ.

Symptomatic breast cancer will be included, as well as screened and interval breast cancer. The breast cancer screening program is public and universal in Spain. Following the recommendations of the European Guidelines for Quality Assurance in breast cancer screening and diagnosis [14], the Spanish Breast Cancer Screening Program provides free biennial screening to women who are between 50 and 69 years old. Recently, women aged from 45 to 49 years and 65 to 69 years are being incorporated into screening programs. Interval breast cancer is defined as primary breast cancer diagnosed in a woman who had a screening test, with or without further assessment, with a negative result, and diagnosed well before the next invitation to the screening test or before a period of time equal to the screening interval in a woman who has reached the upper age limit for screening [15].

Exclusion criteria are: diagnosis of sarcoma, lymphoma or inflammatory carcinoma; breast cancer recurrence; terminal illness; and a severe mental or physical condition or any other factor which interferes with the woman’s ability to complete the questionnaires. In addition, in situ carcinomas will be excluded from the survival analysis.

Socio-demographic and clinical data will be collected on women lost to follow-up. Figure 1 represents flow-chart of the recruitment and Table 2 represents data collection in participant centers.

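### The six-variable limit comes from relapses in all 1456 women, but models are fitted in 60% of them, where relapse supports three; it cannot carry over to other outcomes

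*Protocol article*

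**What the plan says.** The sample size section of the protocol article rests on one rule, "a minimum of 10 outcome events are needed per predictor (relapse"), and on a planned list of predictors described as "likely, not less than 10), in the multivariate regression models". From these it concludes that "we needed at least 100 events of the dependent variable in the sample", taking a 7% relapse rate over two years from the literature. It then reports that relapse has so far run at 4% in 1456 patients, "implying that no more than six variables should be included in the predictive models". No other outcome has an event rate or a variable limit.

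The models themselves are described elsewhere:

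- The Aim section lists prediction models for quality-of-life change, relapse and death. Table 1 adds complications: "To create and validate predictive rules for relapse, mortality and complications".
- The statistical analysis section plans logistic models "when outcome variables are dichotomous (mortality, re-admissions or relapse, major complications"). It adds: "For the continuous outcomes (changes in health-related quality of life), a general lineal model will be used".
- The same section splits participants at random into 60% for derivation and 40% for validation, and builds the model in the derivation group.

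**The concern.** A rule counted in events per predictor gives a different answer for each outcome and for each sample in which a model is fitted. The article applies it once, to one outcome and to the whole cohort. It states the result for the predictive models in general, while the fitting is done in a smaller sample and for several other outcomes.

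A limit set too high for the events available leads to overfitting: unstable coefficients, a score that looks better in derivation than in validation, and poor calibration. This matters because the article intends the rules to become software that informs physicians' and patients' decisions. A limit borrowed from another outcome also gives the remaining models no justification of their own, in either direction.

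**Working it through.** **Inputs.** From the sample size section: 10 events per predictor, 100 target events, 7% planned relapse, 4% observed relapse, N = 1456. From the statistical analysis section: a 60% derivation cohort. Rates for death, readmission and complications are not given, so those below are assumptions that show how the limit moves.

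**1. The plan's own figures.**
- Planned size: 100 / 0.07 = 1428.6, so 1429. This agrees with about 1456 patients, who would give 1456 × 0.07 = 101.9 events.
- Limit: 1456 × 0.04 = 58.24 events; 58.24 / 10 = 5.8, rounded to six. Rounding down gives five.

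The six therefore reproduces, for relapse in all 1456 women.

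**2. Relapse in the sample used for fitting.**
- Derivation cohort: 0.60 × 1456 = 873.6, about 874 women.
- Relapses: 873.6 × 0.04 = 34.9, about 35; 35 / 10 = 3.5, so three variables.
- If the 4% is rounded from anything between 3.5% and 4.5%, relapses run from 30.6 to 39.3, and the answer is still three.
- Six variables on 35 relapses leave 35 / 6 = 5.8 events per variable, not 10.

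**3. Rate at which six variables are supported (60 events).**
- All women: 60 / 1456 = 4.1%.
- Derivation cohort: 60 / 873.6 = 6.9%.

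**4. The same rule at other rates.** Whole variables, rounded down.

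| Two-level outcome rate | Events in 1456 | Variables | Events in 874 | Variables |
|---|---|---|---|---|
| 1% (assumed) | 14.6 | 1 | 8.7 | 0 |
| 2% (assumed) | 29.1 | 2 | 17.5 | 1 |
| 3% (assumed) | 43.7 | 4 | 26.2 | 2 |
| 4% (relapse, observed) | 58.2 | 5 | 35.0 | 3 |
| 7% (relapse, planned) | 101.9 | 10 | 61.2 | 6 |
| 10% (assumed) | 145.6 | 14 | 87.4 | 8 |
| 20% (assumed) | 291.2 | 29 | 174.8 | 17 |
| 30% (assumed) | 436.8 | 43 | 262.2 | 26 |

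Even at the planned 7%, the derivation cohort would have supported six predictors, not the ten intended.

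**5. Change in quality of life.** A linear model has no events, so the rule gives no number. Its capacity depends on how many women complete both questionnaires, and the article gives no response rate. As an illustration, assume that 50% to 100% of the derivation cohort respond (437 to 874 women) and allow 10 to 20 women per variable. The range is then 436.8 / 20 = 21 to 873.6 / 10 = 87 variables.

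**The case against.** The strongest objection is to the reading of the text. The sample size section speaks of a single predictive model, attaches the rule to relapse, and derives six in the same sentence as the relapse rate. The plural could mean the relapse models only, and mortality, readmission, complications and quality of life are not named there. This stands in part: the wording is ambiguous, and it would go too far to say that the article expressly imposes six on every outcome. However, Table 1 and the statistical analysis section use the same term for all these outcomes. If relapse alone was meant, the others have no stated limit. Both readings call for the same clarification, and neither rescues six for relapse in the derivation cohort.

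A second objection is that sizing on one outcome is ordinary practice and that an upper bound of six is merely cautious for common or continuous outcomes. The first half is right, and sizing on relapse is not criticised here. On the second, a tight bound does limited harm, and a reader should not infer that it must yield worse rules: more predictors do not guarantee better validated performance. The point is only that the bound has no derivation for those outcomes.

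Third, the observed 4% is a rate so far, and events will accrue if the five-year follow-up is funded. That is so, but the limit of six is drawn from the present 4%, and on that figure the fitting sample supports three.

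Two stronger inferences are tempting and not supported:

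- That the mortality rule will be overfitted and the complication rule starved of predictors. With no rates in the article, neither can be placed on one side of the break-even.
- That the mortality denominator falls by the 135 stage 0 women in Table 3, since "in situ carcinomas will be excluded from the survival analysis". Mortality is modelled by logistic regression, so equating the two analyses is an inference. The rule also counts deaths, not women, so removing women lowers the limit only by the unknown deaths among them.

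**Conclusion.** The concern holds for two reasons. For relapse, six is about twice what the plan's own rule supports in the derivation cohort: about 35 events and three variables. This uses only the article's own figures and assumes that the relapse rate in the random 60% matches that in the whole cohort.

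For the other binary outcomes, a limit derived from relapse does not transfer. Whether six is too loose or tighter than needed depends on rates that the article does not give. For change in quality of life, an events rule does not apply, whatever the rates.

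This should be corrected before the models are built. It concerns a stated number that the model building relies on. It does not call the size of the cohort into question.

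**What to change.** In the sample size section, replace the single limit by three statements:

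1. For each binary outcome, the maximum number of model coefficients is the number of events of that outcome among the women used to fit the model, divided by 10. Counting coefficients matters because a factor with several categories uses more than one.
2. For relapse at 4%, this is about three if the 60/40 split is kept. It is five to six only if the model is fitted on all 1456 women.
3. The events rule does not apply to the linear quality-of-life models. Their limit rests on the number of women with both the baseline and the two-year questionnaire.

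The cost is a few sentences and no new data. The downside is fewer predictors than now stated for relapse and for any rarer outcome.
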